### Comparison of therapeutic efficacy

The rate of carotid artery restenosis, plaque incidence, and stability of carotid arterial plaque will be analyzed by the chi-square (*χ*^2^) test between the two arms.

The size and thickness of carotid arterial plaque, carotid artery blood flow velocity, blood lipids, hs-CRP, homocysteine, and total bilirubin will be analyzed by *t*-test analysis.

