### Outcomes

Carotid artery restenosis rate

Restenosis is defined as a degree of carotid artery stenosis ≥ 50% by ultrasound examination after CEA, and its proportion in CEA patients is the restenosis rate [1].2)Incidence and properties of carotid plaque

The proportion, size, thickness, and stability of the carotid arterial plaque3)Carotid artery blood flow velocity

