### Interventions

The patients will be allocated to either the experimental or control group based on a blocked randomization sequence generated by SPSS 23.0 software for Windows.

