### Baseline data collection

We will request consent for review of participants’ medical records and for the collection of blood samples to assess blood lipids, hs-CRP, homocysteine, liver function, and kidney function within 1 week before the operation [20]. The blood samples after inspection will be stored in special liquid nitrogen tanks for future use in auxiliary research. On the second day after the procedure, high-resolution-enhanced magnetic resonance imaging (MRI) will be reexamined to understand the recovery of the carotid canal cavity and plaque clearance for subsequent comparison. Carotid artery color Doppler ultrasound will be performed 1 week after the operation to understand plaque.

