### Sample size

The determination of sample size was calculated by SPSS 23.0 software. Based on a previous study and clinical assumptions, carotid restenosis was 5–22% [4–6]. Our previous research showed that the restenosis rate of the carotid artery after CEA in our hospital was approximately 15%. The statistical parameters were set as follows: one-sided log-rank testing with 80% power, the probability of obtaining a false-positive with a statistical test at 0.05, and a 3-year follow-up time. Considering a potential dropout rate of 5% across both groups, it is estimated that 276 patients will need to be enrolled (138 participants per group).

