### Comparison of baseline data

*T*-tests will be performed for quantitative data that are usually distributed, and a nonparametric test will be used for quantitative data that are not normally distributed, including blood lipids, hs-CRP, homocysteine, liver function, and kidney function. The chi-squared (*χ*^2^) test will be used for counting data, including recovery of the carotid canal cavity and plaque clearance. A two-sided *P*-value < 0.05 will be considered statistically significant.

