A consensus has been reached regarding inflammation-mediated intimal hyperplasia, vascular reconstruction, and plaque formation. However, after CEA, the best medical therapy, including inhibition of inflammation, still causes restenosis in many patients [23]. The latest research shows that although there is no nerve distribution in the intima of the blood vessel, the inflammatory reaction in this part is closely related to the nerve axons distributed on the adventitia. By removing this axon, the local inflammatory response can be eliminated, thus effectively inhibiting plaque formation and blocking the arterial stenosis caused by it [16]. Carotid stenosis mainly occurs near the bifurcation, which is just a nerve-rich area, and a small branch distribution of a single carotid sinus nerve. Simply cutting the carotid sinus nerve can achieve the effect of removing the nerve distribution.

We will use the carotid restenosis rate as the main index of the study, and at the same time, we will also select the incidence and properties of carotid plaque; carotid artery blood flow velocity arrhythmia; blood pressure variability; biomarkers for atherosclerosis, such as hs-CRP, homocysteine, and total bilirubin; and blood lipids, such as triglycerides, total cholesterol, high-density lipoprotein, low-density lipoprotein, nonesterized fatty acid, and other research indicators, to comprehensively evaluate the factors related to carotid artery blood supply and plaque formation. Follow-up began in March after the operation and will last for up to 3 years, which is consistent with most of the studies on carotid restenosis carried out at present [4–9]. Therefore, this study intends to observe the carotid restenosis rate, plaque formation, and other indicators after disconnecting the carotid sinus nerve in standard CEA surgery to confirm that this operation can effectively reduce the incidence of carotid restenosis after CEA.

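### The main restenosis test is a valid unadjusted chi-square that makes no use of pre-operative covariates the trial measures anyway; pre-specified adjustment would bring a modest gain, and the baseline significance tests can go.

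*Protocol article*

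**What the plan says.** The Discussion names the main outcome: "We will use the carotid restenosis rate as the main index of the study". The Outcomes section makes it binary: "Restenosis is defined as a degree of carotid artery stenosis ≥ 50% by ultrasound examination after CEA". Under Comparison of therapeutic efficacy the test is fixed: "The rate of carotid artery restenosis, plaque incidence, and stability of carotid arterial plaque will be analyzed by the chi-square" test between the two arms. No covariate-adjusted, stratified or regression analysis appears anywhere in the article.

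Allocation follows a "blocked randomization sequence generated by SPSS 23.0 software" (Interventions). Neither that section nor Randomization and blinding states a stratification factor.

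The Baseline data collection section provides for "collection of blood samples to assess blood lipids, hs-CRP, homocysteine, liver function, and kidney function within 1 week before the operation". Other measures lists LDL cholesterol among the lipids, and Table 1 marks an ultrasound at enrolment. The article gives the baseline values two uses. One is description (Baseline description). The other is a between-arm test at two-sided 0.05 (Comparison of baseline data): a t-test, or "a nonparametric test will be used for quantitative data that are not normally distributed". The same biomarkers at follow-up are separate outcomes.

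**The concern.** Neither the design nor the main analysis uses prognostic information, although candidate covariates are measured before surgery. The Introduction attributes most middle- and late-stage restenosis to atherosclerosis, and Other measures presents these values as atherosclerosis biomarkers, so it is reasonable to think that some of them carry prognostic information. If they do, adjustment would explain part of the outcome variation and largely remove the effect of a chance imbalance on the estimate.

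The tests under Comparison of baseline data do neither. Randomisation already makes their null hypothesis true, so the p-value cannot show whether an imbalance matters for restenosis. What is at stake is a little precision in a trial that expects few events.

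**Working it through.** **Inputs from the article.** Total 276 (138 per arm), 5% dropout, one-sided log-rank at 0.05 with 80% power, 3 years of follow-up (Sample size). For the control rate it says that "the restenosis rate of the carotid artery after CEA in our hospital was approximately 15" percent. Evaluable: 276 × 0.95 = 262, or 131 per arm.

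**The plan's own figure.** The 276 cannot be reproduced, because no experimental rate or hazard ratio is stated; the literature range ("Based on a previous study and clinical assumptions, carotid restenosis was 5–22" percent) does not supply one. It can only be back-solved. With 15% v 6%, HR = ln(0.94)/ln(0.85) = 0.381. Schoenfeld events = 4(1.645 + 0.842)²/(ln 0.381)² ≈ 27. Patients = 27/0.105 ≈ 258, and 258/0.95 ≈ 272. Freedman's formula with 15% v 5.5% gives 278. An experimental rate near 6% is therefore used below as an assumption. A simple chi-square with 131 per arm has 80% one-sided power at 5.7%.

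**Expected events.** 262 × (0.15 + 0.06)/2 ≈ 27, of which the experimental arm contributes 131 × 0.06 ≈ 8.

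**Power of the planned test, 15% v 6%.** The standard error under the alternative is √[(0.15 × 0.85 + 0.06 × 0.94)/131] = 0.0375, and under the null √[2 × 0.105 × 0.895/131] = 0.0379. One-sided: Φ[(0.09 − 1.645 × 0.0379)/0.0375] = 77.0%. Two-sided, with 1.96: 66.3%.

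**With adjustment, by formula.** If the covariates explain a share R² of outcome variance, effective n = 131/(1 − R²).

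| R² (assumed) | One-sided power | Two-sided power |
|---|---|---|
| 0 | 77.0% | 66.3% |
| 0.02 | 77.7% | 67.2% |
| 0.05 | 78.9% | 68.5% |
| 0.10 | 80.8% | 70.9% |
| 0.20 | 84.7% | 75.9% |

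**By simulation, 15% v 6%.** 4,000 trials per setting compared the unadjusted test with a logistic-standardised risk difference using one covariate.

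| Odds ratio per SD (assumed) | R² | Gain, one-sided | Gain, two-sided |
|---|---|---|---|
| 1.5 | 0.02 | 0.4 points | 0.9 points |
| 2.0 | 0.06 | 0.9 | 1.8 |
| 2.7 | 0.12 | 3.5 | 3.7 |
| 4.5 | 0.22 | 6.3 | 10.1 |

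**By simulation, 15% v 5.7%, one-sided, indexed by AUC.** Power went from 81.0% to 81.3% at AUC 0.635, from 81.5% to 83.2% at 0.70, and from 81.8% to 84.5% at 0.75. The variance of the risk difference fell by about 2%, 4% and 10%. A separate run with three covariates gave gains of 0.4, 1.9 and 2.9 points at AUC 0.64, 0.70 and 0.76.

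**Type I error.** With one covariate it was about 5% with or without adjustment. With three covariates it was 5.2% to 6.1% adjusted against 4.8% to 5.8% unadjusted.

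**Chance imbalance.** The standard error of a difference in covariate means is √(2/131) = 0.124 SD. A difference of 0.2 SD or more therefore arises in about 11% of trials (0.2/0.124 = 1.62, p ≈ 0.11), and the planned baseline test would not flag one of exactly 0.2 SD. If the odds ratio were 2.0 per SD, the shift in the risk difference would be about 0.2 × ln 2.0 × 0.092 = 1.3 points, or 1.2 after averaging over the covariate. The factor 0.092 is the mean of p(1 − p) over the arms. The standard error of the risk difference is about 3.7 points.

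**The case against.** The strongest reply is that nothing is wrong. An unadjusted chi-square is valid under randomisation, and its error rate already allows for chance imbalance. That stands. A reader might infer that an imbalance would bias the main result or invalidate the test; the simulated type I error of about 5% does not support that.

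Second, a reader might infer that the trial throws away a material amount of precision. The article does not support that either. It gives no correlation, odds ratio or AUC for these values. Its inflammation argument concerns local, nerve-mediated infiltration of the arterial wall, not systemic hs-CRP. It attributes early restenosis to endothelial injury and remodelling after surgery. Every patient receives a statin afterwards, so pre-operative LDL may not reflect later exposure. Degree of stenosis is restricted by eligibility and measured by mixed methods, and the plaque is then removed. A gain near nil is plausible.

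Third, covariates and model form often sit in an analysis plan, which is not shown here. An adjusted analysis may be specified there. The point survives because the article states specific methods for both the main comparison and the baseline tests, and those stated choices are what is questioned.

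Fourth, the article sizes on a one-sided log-rank test but analyses by chi-square, and mentions a two-sided 0.05 only under the baseline comparison. At 15% v 6%, moving from one-sided to two-sided costs about 11 power points (77.0% to 66.3%), more than weak or moderate covariates would recover. That is a separate and larger matter. It affects the form of the adjusted analysis but does not remove the case for it.

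Unstratified blocking is ordinary in a single-centre trial, and the baseline tests gate no efficacy analysis, so neither is a serious fault in itself.

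**Conclusion.** The point holds as a modest efficiency improvement, not as an error in the planned test. The main comparison makes no use of pre-operative values that the trial measures anyway, and the baseline significance tests are no substitute for using them.

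The expected gain is roughly 0 to 3 power points for weak to moderate covariates (AUC about 0.64 to 0.75), and 6 to 10 points only at R² near 0.22. These figures rest on assumed prognostic strength, a back-solved experimental rate of about 6%, and 131 evaluable patients per arm. The case for dropping the baseline tests depends on none of these assumptions.

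**What to change.** - First settle whether the main analysis is the log-rank test or the chi-square, and at which sidedness.
- Then make the main restenosis analysis a covariate-adjusted marginal risk difference: a logistic model with treatment and covariates, predictions standardised over all randomised patients under each arm, and a robust variance. If time-to-event is chosen, use the adjusted equivalent.
- Use one or two, at most three, pre-operative covariates fixed before unblinding, for example log hs-CRP, LDL cholesterol or the enrolment ultrasound stenosis.
- Exclude the day-2 MRI items (lumen recovery and plaque clearance). The article treats them as baseline data, but they are measured after surgery. The ultrasound one week after surgery is unsuitable for the same reason.
- Report the crude chi-square as supportive.
- Replace the tests under Comparison of baseline data with description by arm.

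The cost is analysis wording only; no new data are needed. The limits are the roughly 27 expected events, about 8 of them in the experimental arm, which argue for the smallest useful covariate set, and a type I error that may run slightly above nominal with three covariates.

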### Follow-up

Follow-up in the outpatient department will be performed every 3 months. At the same time, blood lipids, hs-CRP, homocysteine, liver function, and kidney function will be reexamined after obtaining informed consent. Carotid artery color Doppler ultrasound and carotid artery high-resolution enhanced MRI will be reviewed at 3 months, 6 months, 1 year, 2 years, and 2 years after the operation.

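### Biomarkers and flow velocity are compared by unadjusted t-tests although pre-operative values are collected and the non-normality rule stops at baseline; plaque size has no rule for plaque-free patients

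*Protocol article*

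**What the plan says.** The Comparison of therapeutic efficacy section of the protocol article assigns one method to all continuous outcomes: "The size and thickness of carotid arterial plaque, carotid artery blood flow velocity, blood lipids, hs-CRP, homocysteine, and total bilirubin will be analyzed by" a t-test. It names no covariate, visit, transformation or rank alternative.

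Other sections show what data will be available:

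- **Pre-operative values.** Baseline data collection provides for "the collection of blood samples to assess blood lipids, hs-CRP, homocysteine, liver function, and kidney function within 1 week before the operation". Table 1 also marks colour Doppler, high-resolution MRI and the atherosclerosis biomarkers at enrolment. Total bilirubin is not named in the baseline text, but Other measures lists it among those biomarkers.
- **Early post-operative scans.** "On the second day after the procedure, high-resolution-enhanced magnetic resonance imaging (MRI) will be reexamined", and a Doppler follows at 1 week. Both come after the nerve has been cut in the experimental arm.
- **Repeated follow-up.** Bloods are rechecked at outpatient visits: "Follow-up in the outpatient department will be performed every 3 months". Table 1 shows five follow-up times for bloods and imaging, the last at 3 years. The Follow-up text says that imaging "will be reviewed at 3 months, 6 months, 1 year, 2 years, and 2 years after the operation", which repeats 2 years where Table 1 has 3.
- **Non-normality.** Under Comparison of baseline data, "a nonparametric test will be used for quantitative data that are not normally distributed", with lipids, hs-CRP and homocysteine listed. The section on therapeutic efficacy has no such rule.
- **Plaque.** Incidence and stability are tested by chi-square, size and thickness by t-test. Nothing says how a patient without plaque enters the t-test. The Statistical analysis section makes intention-to-treat the main form of analysis.

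**The concern.** The test is a stated choice, so this is not a detail left to a fuller plan. It has three weaknesses.

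First, a pre-operative value that predicts the outcome is available at no extra cost and is left out. The comparison is then less precise than the data allow.

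Second, the article foresees non-normality in lipids, hs-CRP and homocysteine, but acts on it only in the baseline table, where little depends on it. The same markers get only a t-test when they are outcomes.

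Third, surgery removes plaque in both arms and plaque incidence is itself an outcome, so some patients will have no plaque to measure. If size and thickness were compared only among those with plaque, the compared groups would be formed by something that happens after randomisation and that the procedure is meant to change.

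At stake is the power to see an effect on the biomarkers and on velocity, and a clear meaning for the plaque-size result.

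**Working it through.** The article gives no power figure for these outcomes. Its 276 patients relate to restenosis and serve here only to set the number of evaluable patients.

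**Inputs**
- 138 per arm and 5% dropout (Sample size): 138 × 0.95 = 131 evaluable per arm.
- Two-sided 0.05, stated for baseline comparisons and assumed here for the outcomes.
- Baseline-outcome correlation ρ: not in the article; 0.3, 0.5 and 0.7 assumed.
- Skewness: not in the article; lognormal data with log-scale SD 0.8, 1.0 and 1.2 assumed.

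**Step 1: plain t-test.** The difference detectable with 80% power is (1.9600 + 0.8416) × √(2/131) = 0.346 SD.

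**Step 2: baseline adjustment.** ANCOVA multiplies the variance by 1 − ρ². Power at the same difference is Φ(2.8016/√(1 − ρ²) − 1.9600).

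| ρ | 1 − ρ² | Power | Equivalent t-test n per arm, 131/(1 − ρ²) |
|---|---|---|---|
| 0.3 | 0.91 | Φ(2.937 − 1.960) = 83.6% | 144 |
| 0.5 | 0.75 | Φ(3.235 − 1.960) = 89.9% | 175 |
| 0.7 | 0.51 | Φ(3.923 − 1.960) = 97.5% | 257 |

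The upper rows are the safer guide for velocity. The enrolment Doppler is taken through a stenosis that surgery then removes, so the correlation may be low.

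**Step 3: skewness.** Simulation with 131 per arm and 20,000 runs, with a multiplicative effect set to give 80% power on the log scale:

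| Log-scale SD | Type I error, raw t-test | Power, raw t-test | Power, log scale |
|---|---|---|---|
| 0.8 | 4.8% | 67% | 80% |
| 1.0 | 4.7% | 60% | 80% |
| 1.2 | 4.2% | 52% | 80% |

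Type I error does not rise above 5%. The cost of ignoring skewness is power.

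**Step 4: plaque size.** This illustration has invented inputs. Severity is lognormal with log-scale SD 0.5, plaque is present in 50% of controls and 30% of treated patients, and treatment prevents the mildest plaques and enlarges none. Mean size among patients with plaque is 1.57 in controls and 1.85 in treated patients, so the treated arm looks worse. Counting plaque-free patients as zero gives 0.50 × 1.57 ≈ 0.78 against 0.30 × 1.85 ≈ 0.56, so the treated arm looks better. The direction of the result can depend on a rule that the article does not state.

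**The case against.** The strongest reply is that an unadjusted t-test is a valid test in a randomised trial. Chance baseline imbalance is already covered by its standard error, and Step 3 shows no inflation of type I error. Baseline adjustment is then advice on efficiency. This stands, and it limits the point to lost power. The outcomes are also not primary: the Discussion names restenosis as the main index, and Other measures holds the biomarkers. The abstract does list plaque and flow velocity among its main indices, so they are not trivial either.

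Three stronger readings are tempting, and the article does not support them:

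- A reader might infer that the plaque comparison is non-randomised. The article does not restrict it to patients with plaque, and its intention-to-treat statement points the other way. With zeros for plaque-free patients the comparison stays randomised. Plaque incidence is also tested separately, so a preventive effect could show there.
- A reader might infer a separate t-test at every visit, with the multiplicity that brings. No visit is named, so per-visit testing is neither planned nor excluded.
- A reader might take the lipids and inflammatory markers as known to be skewed. The article only says that normality will be determined.

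It is also fair to object that the power gains rest on assumed correlations. They do, and the range is shown for that reason.

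**Conclusion.** The point holds as a loss of efficiency and a gap in one rule, not as an invalid analysis. The stated t-tests leave out pre-operative values that the trial collects, and the article's own provision for non-normal markers is not carried from baseline to outcome.

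For assumed correlations of 0.3 to 0.7, adjustment would raise 80% power to between about 84% and 97.5%, with velocity probably gaining least. For the assumed degrees of skewness, the raw t-test has 52% to 67% power where the log scale has 80%. These sizes depend on correlations and distributions that the article does not give; their direction does not.

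For plaque size and thickness, the supportable finding is that a comparison limited to patients with plaque is left open. The restenosis comparison is not affected.

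**What to change.** Change the wording under Comparison of therapeutic efficacy:

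- **Lipids, hs-CRP, homocysteine, total bilirubin, flow velocity.** Replace the t-test by ANCOVA at 3 years, or a mixed model over visits that reports the 3-year contrast, adjusted for the pre-operative value. State that bilirubin is measured before surgery.
- **Velocity covariate.** Use the enrolment Doppler only. The day-2 MRI and 1-week Doppler follow randomisation and nerve transection, so adjusting for them could remove part of an early effect. Using the enrolment scan only where a post-operative one is missing would mix values from before and after endarterectomy.
- **Non-normal markers.** Extend the baseline rule to the outcomes by log transformation or a rank analysis, chosen for each marker before unblinding. A log analysis reports a ratio of geometric means.
- **Plaque size and thickness.** Analyse all randomised patients by a rank test, with zero where the scan shows no plaque. A missing scan is not a zero.
- **Visit schedule.** Reconcile the repeated 2-year entry in the Follow-up text with the 3-year visit in Table 1, since the reported contrast depends on it.

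The cost is wording and a little analysis time. SPSS fits these models, and no new data or patients are needed.

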### Safety evaluation

The incidence of adverse events (arrhythmia, blood pressure variability) will be expressed as the number of patients (percentage) and analyzed by the chi-square (*χ*^2^) test.

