**Method/design:**

This study is a randomized, double-blind, single-center study. We will recruit 276 patients, who will be randomly divided into the experimental group and the control group. Based on the standard CEA operation, the operator will search for the carotid sinus nerve on the surface of the internal carotid artery and will entirely transect it in the experimental group. Both groups will be guided with the same postoperative treatment and will be followed up every 3 months for 3 years after the operation. The main indices observed will be the carotid restenosis rate, incidence and nature of carotid plaque, and carotid blood flow velocity. Other indices will be arrhythmia, blood pressure variability, and biomarkers of atherosclerosis, such as blood lipids, hypersensitive C-reactive protein (hs-CRP), homocysteine, and total bilirubin.

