### Other measures

These are arrhythmia; blood pressure variability; biomarkers for atherosclerosis, such as hs-CRP, homocysteine, and total bilirubin; and blood lipids, such as triglycerides, total cholesterol, high-density lipoprotein, low-density lipoprotein, and nonesterified fatty acids [19].

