### Reports of adverse events

Adverse events (AEs) will be assessed primarily by electrocardiogram and blood pressure monitoring. The occurrence, severity level, management strategies, causality related to the experimental surgery, and termination of all adverse events (AEs) will be recorded and preserved during the clinical trials and follow-up. All severe adverse events (serve arrhythmia) will be reported promptly to the principal investigator and the research ethics committee (REC). The researchers and clinical trial institutions will ensure that the subjects are treated appropriately and informed truthfully of the relevant information. According to China’s Management Specification for Classification and Sort of Surgical and Invasive Procedures in Medical Institutions, researchers are responsible for the cost of dealing with adverse reactions and compensation for patients who suffer adverse reactions. Participants are not provided with specific posttrial care (Table 1).

**Table 1 Tab1:** The flow diagram of enrollment, allocation, interventions, and follow-up for participants

	Enrollment	Allocation	Intervention		Follow-up				
			CEA	neurectomy	3 M	6 M	1 Y	2 Y	3 Y
Timepoint	1 week	0	1 week		3 years				
Enrollment									
Eligible screen	×								
Informed consent	×								
Demographic & medical data	×								
Random allocation		×							
Interventions									
Experimental group			×	×					
Control group			×						
Assessments									
Color Doppler ultrasound	×				×	×	×	×	×
HRMR	×				×	×	√	√	×
ECG	×				×	×	×	×	×
Biomarkers for atherosclerosis	×				×	×	×	×	×
Adverse events					×	×	×	×	×

*CEA* carotid endarterectomy, *HRMR* high-resolution enhanced nuclear magnetic resonance, *ECG* electrocardiogram, *M* month, *Y* years

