## Discussion

There is considerable controversy about the treatment of restenosis after CEA, and there is a lack of relevant guidelines. Doctors must rely on the degree of stenosis, clinical symptoms, and vascular compensation to make clinical decisions [11]. Some methods are used to perform CEA surgery or CASI treatment again. Nevertheless, according to different research reports, it may be dangerous to perform CEA or CASI on restenosis patients [7]. Scar tissue makes it more challenging to redo CEA, and CASI cannot achieve an excellent therapeutic effect. A study showed that the probability of intrastent restenosis in patients treated with CASI may reach 24% within 4 years [21].

Before this, carotid sinus denervation was used to treat carotid sinus syndrome, hypertension, heart failure, and other diseases, and its safety has been confirmed. In the treatment of carotid sinus syndrome, researchers found that the carotid sinus can be denervated by peeling off the adventitia 3 cm from the proximal end of the internal carotid artery. By injecting lidocaine into the carotid sinus for anesthesia, the blood pressure and heart rhythm of patients can be kept stable during the operation, with no significant fluctuation in systolic blood pressure, diastolic blood pressure, or heart rhythm observed after the process [19]. Others have shown that removing the carotid sinus nerve for the treatment of essential hypertension will not reduce the blood pressure of rats, while removing the bilateral carotid sinus nerve can reduce the blood pressure of hypertensive rats by 20 mmHg, which also shows that unilateral carotid sinus nerve removal will not affect blood pressure in this study [22].

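### Blood pressure variability, one of two named safety comparisons, is analysed only as a count of patients with no stated event threshold, and Table 1 has no blood pressure row

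*Protocol article*

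**What the plan says.** Blood pressure variability appears in the abstract ("Other indices will be arrhythmia, blood pressure variability, and biomarkers of atherosclerosis"), under Other measures ("These are arrhythmia; blood pressure variability; biomarkers for atherosclerosis") and again in the Discussion's list of indicators.

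Its only stated analysis is in Safety evaluation: "The incidence of adverse events (arrhythmia, blood pressure variability) will be expressed as the number of patients (percentage"), compared by chi-square. Arrhythmia is the only other item named there.

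On measurement, Reports of adverse events says: "Adverse events (AEs) will be assessed primarily by electrocardiogram and blood pressure monitoring". Table 1, in the same section, marks ECG at enrolment and at 3 months, 6 months, 1, 2 and 3 years. It has no blood pressure row. Its Adverse events row is marked at the same five follow-up points, but not at enrolment or in the intervention columns. Baseline data collection covers "the collection of blood samples to assess blood lipids, hs-CRP, homocysteine, liver function, and kidney function within 1 week before the operation", plus imaging. Follow-up says that "blood lipids, hs-CRP, homocysteine, liver function, and kidney function will be reexamined", again with imaging. Neither mentions blood pressure.

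The Discussion, reasoning from a rat study, says that "unilateral carotid sinus nerve removal will not affect blood pressure in this study".

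**The concern.** The experimental step cuts the nerve that serves a pressure receptor, as the Introduction explains, so blood pressure is the function most directly exposed to the intervention. The variable chosen to watch it does not match its stated analysis. Arrhythmia can be counted as present or absent. Variability cannot, until someone fixes how it is calculated and where it becomes an event. Without that, the numerator of the percentage depends on what each assessor happens to record.

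Two things are at stake. First, the comparison discards information even if a threshold is supplied later. Second, an undefined, low-power comparison is likely to give no significant difference unless the effect is large. Next to the Discussion's sentence on blood pressure, such a result could be taken as reassurance that it does not provide.

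**Working it through.** **Step 1. Does the analysis fit the variable?** Comparison of therapeutic efficacy splits its variables by type. Restenosis, plaque incidence and plaque stability go to chi-square. Plaque size and thickness, flow velocity, lipids, hs-CRP, homocysteine and total bilirubin go to a t-test. Blood pressure variability is in neither list; it appears only in Safety evaluation, as a patient count. The authors therefore do use continuous methods for continuous measures, and this measure was left out.

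**Step 2. Is there a data series to derive it from?** The two tools named for adverse events are treated differently in Table 1:

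| | Enrolment | Intervention columns | 3 M to 3 Y |
|---|---|---|---|
| ECG row | marked | blank | 5 marks |
| Blood pressure row | no row | no row | no row |
| Adverse events row | blank | blank | 5 marks |

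If blood pressure is read as part of the Adverse events row, it is assessed at five follow-up points, with no mark before surgery or in the intervention columns and no stated number of readings.

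**Step 3. What does a yes/no analysis cost?** The article gives no figure for blood pressure variability, so there is none to reproduce, and what follows is illustrative. Inputs from Sample size: 138 per group and 5% dropout, giving 138 × 0.95 = 131.1, about 131 evaluable per arm. Assumptions: two-sided α = 0.05 (z = 1.96), a normally distributed measure, a true between-arm shift of d = 0.35 SD, and control event rates of 5%, 10%, 20% or 50%.

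Continuous comparison: power = Φ(d√(n/2) − 1.96) = Φ(0.35 × √65.5 − 1.96) = Φ(2.83 − 1.96) = Φ(0.87) = 81%.

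Yes/no comparison: for control rate p₁, the cut-point is c = Φ⁻¹(1 − p₁) and the experimental rate is p₂ = 1 − Φ(c − d). Power = Φ{[(p₂ − p₁) − 1.96·SE₀]/SE₁}, where SE₀ = √[2p̄(1 − p̄)/n], p̄ is the mean of p₁ and p₂, and SE₁ = √{[p₁(1 − p₁) + p₂(1 − p₂)]/n}.

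| Control rate p₁ | Experimental rate p₂ | Power |
|---|---|---|
| 5% | 9.8% | 31% |
| 10% | 17.6% | 43% |
| 20% | 31.1% | 54% |
| 50% | 63.7% | 61% |

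Example at p₁ = 5%: SE₀ = 0.0323 and SE₁ = 0.0322, so (0.0477 − 1.96 × 0.0323)/0.0322 = −0.49, and Φ(−0.49) = 31%.

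The pattern is the same for other shifts. At 0.25 SD, power is 53% continuous against 18% to 36% yes/no; at 0.5 SD, 98% against 59% to 89%.

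**Step 4. What could the yes/no analysis detect?** With 131 per arm and 80% power, the detectable contrasts are 5% against 15.5%, 10% against 22.8%, and 20% against 35.5%.

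**The case against.** - **Blood pressure is monitored.** A reader might infer from Table 1 that no blood pressure is ever taken. The text does not support that: monitoring is named for adverse events, that row is marked at five visits, and the Surgical treatment section manages pressure relative to a basal level, so a basal value is known. What stands is narrower: there is no dedicated row, and no baseline entry or number of readings from which variability could be derived.
- **It is not a trial hypothesis.** A reader might also infer that the trial sets out to show blood pressure is unaffected and cannot. The sentence is an inference in the Discussion; the stated aim is restenosis, and no equivalence objective on blood pressure is set. Nor is the test powerless: with a defined event, chi-square could reveal a large difference. The article's safety rationale is also not limited to rats, since the Introduction and Discussion cite patients treated for carotid sinus syndrome, although by a different procedure.
- **A baseline is not essential.** In a randomised comparison, post-operative values can be compared without one. That is correct; the baseline adds precision.
- **Details may sit elsewhere.** A threshold, device or number of readings may be in the full protocol, which is not shown, and their absence alone would be no finding. The point rests instead on what the article states: a patient-count analysis for a continuous measure, and a schedule that treats the two named tools unequally.
- **The power figures are generic.** They depend on an assumed shift and assumed cut-points, and are not a measured loss in this trial.

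**Conclusion.** The point holds as a mismatch between a listed measure, its stated analysis and the assessment schedule. On the article's text, the comparison is undefined, because no threshold turns variability into an event, and inefficient, because a continuous quantity is reduced to yes or no. The illustrative loss at a 0.35 SD shift is from about 81% power to between 31% and 61%, assuming normality, two-sided α = 0.05, 131 evaluable per arm and control event rates of 5% to 50%. A non-significant result would therefore be weak evidence about any effect on blood pressure. The primary restenosis analysis, the sample size and the interim rule are untouched.

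**What to change.** 1. Add a blood pressure row to Table 1 at enrolment, during the 2-week inpatient stay and at each follow-up visit, with a fixed number of readings each time. Bring Baseline data collection and Follow-up into line.
2. In Safety evaluation, define variability as a within-patient quantity, for example the SD or coefficient of variation of systolic pressure over a stated set of readings.
3. Compare it between arms as a continuous outcome adjusted for the baseline value, and report the difference with a confidence interval.
4. Count blood pressure adverse events separately, with a stated definition, and keep the chi-square test for those.

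The cost is a few extra cuff readings and CRF fields at contacts already planned, plus a short change to the analysis text. Trial status reports 13 patients recruited; these and any enrolled before the change may lack a standardised baseline, and the analysis should say how they are handled.
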